## Abstract

**Introduction:**

Total knee arthroplasty (TKA) is a widely-used treatment for end-stage knee osteoarthritis. However, it is common for patients to experience issues with knee joint function and abnormal gait following the surgery. Previous studies have primarily focused on concentric contraction of the quadriceps during TKA, neglecting the potential benefits of eccentric isokinetic training for the hamstrings. This protocol outlines a randomized, single-blind, controlled trial aimed at assessing the impact of eccentric isokinetic training for the hamstring muscles on pain, function, and gait in patients after TKA.

**Methods and analysis:**

Fifty participants between the ages of 50 and 80 with knee osteoarthritis undergo unilateral total knee arthroplasty (TKA) for the first time. They will be transferred to the rehabilitation department 10–14 days after the operation. The participants are randomly divided into two groups, with 25 participants in each group: the control group and the Hamstring training group. The Control group will receive routine rehabilitation treatment, while the Hamstring training group will receive a combination of routine rehabilitation treatment and isokinetic eccentric training of the hamstring. The intervention will last four consecutive weeks. Both groups will be assessed at three different times: before the intervention, after 4 weeks of intervention, and 4 weeks after the interventions (follow-up). The primary outcome will be functional capacity (TUGT) and Hospital for Special knee Score (HSS). Secondary outcomes will be knee-related health status (isokinetic knee position perception, Peak torque of hamstring strength), pain intensity (Visual analog scale, VAS) and 3D gait analysis.

**Discussion:**

The study aims to provide relevant evidence on the effectiveness of eccentric hamstring muscle contraction training in improving knee joint function and walking function after TKA.

**Clinical trial registration:**

https://www.chictr.org.cn/showproj.html?proj=195544, Identifier ChiCTR2300073497.

## Introduction

Knee osteoarthritis is a chronic joint disease mainly occurring in middle-aged and older adults. The incidence rate of knee osteoarthritis is increasing due to the aging of the population, which is causing a significant economic burden on society (1, 2). Total Knee Arthroplasty (TKA) is a prevalent intervention for managing end-stage knee osteoarthritis, primarily in the aging population, which significantly alleviates pain and improves joint function (3). Despite the surgery’s effectiveness, many patients post-TKA experience persistent challenges in regaining optimal knee function and a normal gait pattern (4). Current rehabilitation protocols predominantly focus on the quadriceps and largely employ concentric muscle training strategies (5, 6). This conventional approach, while beneficial, often fails to address the full spectrum of functional recovery (7), particularly in the eccentric control of the hamstring muscles, which play a crucial role in joint stability and gait dynamics.

The activation pattern of the muscles of the lower extremities, which relies on muscle synergy, changes with age. The activation of hamstring muscle cooperative activity in older adults over 60 is about 1.6 times that of young people during daily activities. The activity of muscles around the ankle joint in these individuals is also relatively higher (8). As a result, the importance of hamstrings in human sports increases with age. For the functional recovery of early patients after TKA, the increase in hamstring activity is a natural choice of the body. It can stabilize the knee joint by increasing pressure (9), improve eccentric control of the load, and increase the protection of ligaments around the knee joint during standing phase (10). It is a natural compensatory adaptation of the body to weakness, pain, and local environmental changes in the quadriceps femoris (11). This is not a “bad adaptation,” but the body’s coping mechanism for maintaining function and managing pain.

Concentric contraction is used primarily in hamstring muscle strength training rather than eccentric contraction. However, compared to concentric contraction training, Eccentric training is known for its superior efficacy in enhancing muscle strength, improving joint stability, and increasing the resilience of muscle tendons (12). This form of training could potentially offer substantial improvements in the functional recovery phases following TKA. However, the specific benefits of eccentric hamstring training in post-TKA rehabilitation remain underexplored and poorly documented in the existing literature.

Our study aims to bridge this gap by conducting a comprehensive analysis of isokinetic eccentric training for the hamstrings on knee function and gait rehabilitation post-TKA. We hypothesize that incorporating eccentric hamstring exercises into the postoperative rehabilitation protocol will result in better functional outcomes compared to traditional methods focusing solely on the quadriceps. This study aims to furnish concrete proof that endorses a comprehensive strategy for muscle training during TKA recovery, which could transform existing rehabilitation methodologies by prioritizing the equilibrium of muscle forces and the refinement of joint mechanics.

## Methods

### Aims

The study will explore the effect of hamstring isokinetic eccentric training on early lower limb motor function recovery in patients after TKA. Mainly includes: Comparing the effects of hamstring isokinetic eccentric contraction training on the affected side hamstring muscle strength, knee joint position sense, knee joint function score and three-dimensional gait in patients with early TKA surgery; analysis and discussion of hamstring isokinetic eccentric contraction training Effects of contraction training on knee joint muscle strength, proprioception and walking function in patients with TKA.

### Trial design

This study is a prospective randomized controlled trial. The study will be developed in Four stages, according to Figure 1. The eligible participants will be recruited from The Second Rehabilitation Hospital of Shanghai. The doctor in the rehabilitation medicine department of the hospital informed the eligible patients of the research plan. All participants provided their written informed consent. Baseline evaluation will include assessment of name, sex, height, weight, age, and affected limb. After random assignment to different intervention groups, participants will enter the intervention phase. This phase will consist of two different intervention programs lasting 4 weeks. The outcome indexes will be evaluated before intervention, after 4-Week intervention and after 4 weeks follow-up. This study follows the CONSORT statement (13) and the ethical principles of the Declaration of Helsinki.

**Figure 1 fig1:**
[figure not shown]
Design and flow of participants through the trial.

### Participants and setting

Individuals after TKA will be recruited between August 2023 and August 2025 at Shanghai second Rehabilitation Hospital. At least fifty participants will be included in this study.

### Inclusion criteria

Were aged between 50 to 80 after TKA.Had knee osteoarthritis and received unilateral TKA for the first time and was transferred to the rehabilitation department 10–14 days after the operation.During the 10–14 days postoperative period, participants did not engage in strength training related to the quadriceps and hamstrings.Were operated with the same type of posterior stabilized prosthesis;Were able to cooperate with rehabilitation training.Had no regular exercise habits.Provided written informed consent.

### Exclusion criteria

Postoperative complications include infection, neurovascular injury, or symptomatic deep vein thrombosis.History of ipsilateral hip replacement, osteoarthritis, or pain of ipsilateral hip.Severe comorbidities include lower limb fracture, malignant tumor, cardiovascular disease, or neurological disease.Other reasons for exclusion (mentally unable to participate, etc.).

After randomization, the criterion for dropping out will be the participants not attending the assessments (4 weeks, and follow-ups).

### Sample size

Based on the work being done by the team when formulating the plan, we estimated that the difference in TUGT time between the two groups was 1.87 s. With a 2-sided α error of 0.05 and a β error of 0.20, the sample size is estimated at 22 patients in each group. Due to a dropout rate of about 10%, 50 patients are needed.

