### Randomization procedure and concealment of allocation

Patients who meet the inclusion criteria and are willing to participate will be randomized in a 1:1 allocation ratio after the baseline assessment. SPSS25.0 (IBM Corp., Armonk, NY, United States) statistical software was used to generate random serial numbers. These serial numbers were then printed on cards, sealed in paper envelopes, and the same serial number was written on the outside of each envelope. Patients opened the envelopes in the order of their recruitment. The participants will be randomly divided into two groups: the experimental group (hamstring training group) consisting of 25 cases, and the control group (routine rehabilitation group) consisting of 25 cases. The allocation numbers were concealed in opaque sealed envelopes prepared by a central study coordinator. These envelopes will only be accessible to the central study coordinator, who will open them after obtaining informed consent and baseline measures.

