#### Statistical analysis

SPSS24.0 statistical software was used for the statistical analysis of the data in this study. Data were presented as mean (SD) or median [Q1–Q3] for quantitative variables and frequency (%) for categorical variables. The design includes two groups and three time points. The Shapiro–Wilk test is used to check the normality of the measurement data; if the data do not follow a normal distribution, transformations will be applied. A two-way ANOVA is conducted to determine whether there is an interaction between group and time factors. If an interaction is detected, we will assess whether time or group has an independent effect. If no interaction is detected, we will determine if there are any main effects. Post-hoc comparisons between groups at the same time points are adjusted using Bonferroni correction to ensure the overall type I error rate for each ANOVA does not exceed 0.05. Minimal clinically significant differences (MCID) were applied to compare the present results. The analyzes were conducted intention-to-treat by an independent statistician blinded to group allocation. The significance level is set at α = 0.05.

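### The trial is sized for one unadjusted TUGT comparison at alpha 0.05, but the analysis Bonferroni-corrects the between-group comparisons, so the stated 80% power is not shown for the tests planned

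*Protocol article*

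**What the plan says.** **Protocol article, Sample size.** The effect is one between-group difference in TUGT, with no visit attached: "we estimated that the difference in TUGT time between the two groups was 1.87 s". The error rates and result follow: "With a 2-sided α error of 0.05 and a β error of 0.20, the sample size is estimated at 22 patients in each group". No multiplicity adjustment is mentioned. The allowance for losses is "Due to a dropout rate of about 10%, 50 patients are needed".

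**Protocol article, Statistical analysis.** The design has two groups and three time points. A two-way ANOVA tests the group-by-time interaction, and main effects are examined if no interaction is found. For the visit-specific tests, "Post-hoc comparisons between groups at the same time points are adjusted using Bonferroni correction", with the aim of holding the type I error of each ANOVA at 0.05. The section does not say how many comparisons share the correction, and no section names a primary visit for TUGT.

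**Protocol article, Randomization procedure.** Patients are "randomized in a 1:1 allocation ratio after the baseline assessment", so the first of the three time points precedes allocation.

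**The concern.** The alpha in the sample-size calculation is not the alpha at which the plan tests a between-group TUGT difference at a visit. Three time points give three such comparisons and a threshold of 0.05/3 = 0.0167 each. One of the three is baseline, where randomisation rules out a treatment effect, so a third of the alpha is spent where nothing can be found.

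At stake is how the result is read. If the assumed 1.87 s effect is real, the sample-size section puts the chance of missing it at 20%. For a given visit under the correction, that chance is nearer 29–35%. A non-significant result would then be judged against a power that the planned visit-specific tests do not have.

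**Working it through.** **Inputs from the protocol article**
- Difference in TUGT: 1.87 s (Sample size).
- Two-sided alpha 0.05 and power 0.80 (Sample size).
- 22 evaluable per group; about 10% dropout; 50 in total (Sample size).
- 1:1 allocation (Randomization procedure).
- Three time points, with Bonferroni correction within each ANOVA (Statistical analysis).

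The SD is not stated. I therefore take n = 22 as given and back-solve the effect size.

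**Step 1. Reproduce the plan's figure.** For a two-sample t test with n per group, the noncentrality is d × √(n/2), with 2n − 2 degrees of freedom. Setting power to 0.80 at n = 22 and alpha 0.05 gives d = 0.865, that is, an SD of 1.87/0.865 = 2.16 s. The figure of 22 is consistent with one unadjusted comparison. The dropout step also reproduces: 22/0.9 = 24.4, so 25 per group and 50 in total.

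**Step 2. Power for a given visit under Bonferroni.** Hold d = 0.865 and change only alpha.

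| Comparisons corrected | Alpha each | 22 per group | 25 per group |
|---|---|---|---|
| 1 (as sized) | 0.05 | 80.0% | 85.0% |
| 2 (post-baseline visits only) | 0.025 | 70.5% | 76.9% |
| 3 (literal reading, baseline included) | 0.0167 | 64.6% | 71.6% |

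**Step 3. Check that does not need the SD.** Under the normal approximation, power = Φ(z₀.₉₇₅ + z₀.₈₀ − z₁₋α/₂), where z₀.₉₇₅ + z₀.₈₀ = 1.960 + 0.842 = 2.802.
- Alpha 0.025: Φ(2.802 − 2.241) = Φ(0.560) = 71.2%.
- Alpha 0.0167: Φ(2.802 − 2.394) = Φ(0.408) = 65.8%.

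The loss of power therefore does not hinge on the unstated SD.

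**Step 4. The whole analysis path.** This needs assumptions that the document does not supply. I simulated 22 per group with d = 0.865 at 4 weeks, equal variances and a common between-visit correlation of 0.3 to 0.7. Success meant a significant interaction plus a significant comparison at either post-baseline visit (alpha 0.0167) or, without an interaction, a significant group main effect.
- Same effect at follow-up as at 4 weeks: about 77–85%.
- Effect halved or gone by follow-up: about 62–68%.

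**Step 5. Power of the proposed test.** For a baseline-adjusted comparison at 4 weeks, the effective effect size is d/√(1 − ρ²), where ρ is the baseline-to-4-week correlation (assumed), with 41 degrees of freedom.
- ρ = 0.3: 0.865/√0.91 = 0.906; power 83.5%.
- ρ = 0.5: 0.865/√0.75 = 0.998; power 89.8%.

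**The case against.** The Bonferroni comparisons are described as post hoc. They sit behind an interaction test, with a main-effects route if that test is not significant, and no single visit is declared decisive. A difference at either post-baseline visit could count as success, and Step 4 shows that power may then reach or exceed 80% if the effect persists. This stands. A reader might infer that the trial's power is 65%; the document does not support that. The 65% applies to one given visit, three corrected comparisons and 22 evaluable per group. The number three is itself inferred from the number of time points.

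Other stronger readings also fail:
- **That the sample-size arithmetic is wrong.** It is not: 22 and 50 are consistent with the stated inputs and a plausible SD. The fault lies between two sections.
- **That power is cut further because TUGT and HSS are both primary.** The plan controls error within each ANOVA and nowhere splits alpha across the two outcomes.
- **That the missing SD and the absence of an HSS calculation are defects in themselves.** A journal article may leave both to the full protocol.

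The objection does not restore the stated figure. Neither count of corrected comparisons gives 80% for a given visit, even with no dropout (72% or 77%). The document also states neither an either-visit success rule nor the effect pattern and correlation needed to work out its power.

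**Conclusion.** The concern holds as an inconsistency between the sizing and the analysis. It should be fixed, but it does not invalidate the design. The stated beta of 0.20 belongs to one unadjusted TUGT comparison that the plan does not single out. For a given visit with 22 evaluable per group, power is about 65% with three comparisons corrected or 71% with two; with 25 per group it is 72% or 77%. These figures rest on the effect size implied by n = 22 and on two-sample comparisons. If the comparisons are run only after a significant interaction, power for a given visit cannot be higher than this. For success at either post-baseline visit, power is about 62–85% under the assumed patterns, on both sides of 80%. The right statement is that 80% is not shown for the planned analysis, not that it is certainly missed.

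**What to change.** Before the data are analysed, name the baseline-adjusted between-group TUGT difference at 4 weeks as the one primary TUGT test, at two-sided alpha 0.05. Take baseline out of the Bonferroni family and make the 4-week follow-up comparison secondary. With 22 evaluable per group, this gives about 83% power at an assumed baseline correlation of 0.3 and 90% at 0.5.

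The cost is a change of wording in the Sample size and Statistical analysis sections, with no extra patients or visits. The small downside is that the follow-up comparison loses primary status.

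If the Bonferroni plan is kept, state how many comparisons it covers, drop baseline from them, and restate power as about 71% per visit (about 65% if baseline stays). Keeping 80% per visit instead would need 27 evaluable per group for two comparisons (27/0.9 = 30 per group, 60 in total) or 30 for three (30/0.9 = 33.3, so 34 per group, 68 in total).

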### Recruitment procedure

Patients who meet the inclusion criteria and are receiving treatment at The Second Rehabilitation Hospital of Shanghai will be invited to participate in the RCT study. To ensure maximum recruitment, doctors, evaluators, and physiotherapists involved in the recruitment process have received training and instructions. The recruiting doctor will provide participants with both oral and written information about the study. If the participant or their guardian agrees to participate in the study, they will be required to sign a written informed consent.

### Randomization procedure and concealment of allocation

Patients who meet the inclusion criteria and are willing to participate will be randomized in a 1:1 allocation ratio after the baseline assessment. SPSS25.0 (IBM Corp., Armonk, NY, United States) statistical software was used to generate random serial numbers. These serial numbers were then printed on cards, sealed in paper envelopes, and the same serial number was written on the outside of each envelope. Patients opened the envelopes in the order of their recruitment. The participants will be randomly divided into two groups: the experimental group (hamstring training group) consisting of 25 cases, and the control group (routine rehabilitation group) consisting of 25 cases. The allocation numbers were concealed in opaque sealed envelopes prepared by a central study coordinator. These envelopes will only be accessible to the central study coordinator, who will open them after obtaining informed consent and baseline measures.

### Blinding

This study used the single-blind principle. The investigator responsible for the patient assignment was uninvolved in-patient recruitment, evaluation, treatment, and data statistics. The study evaluators were unaware of the allocation of patients. No blinding could be performed by the physical therapy staff or the patients.

### Rehabilitation interventions

Patients will be randomized to one of two treatments initiated as soon as possible after randomization. Both groups of patients received routine rehabilitation treatment, including manual therapy, quadriceps femoris, calf muscle strength training, knee joint flexibility and range of motion training, walking, and stair climbing (14). 40 minutes per day, five days per week, for a total of four weeks.

### Control group

The patients in the control group were given routine rehabilitation treatment:

Body position: the affected knee was kept straight.Isometric contraction training of the anterior and posterior muscle groups of the knee joint: 10 s contraction, 10 s relaxation, 10 times per group, three groups per day.Ankle pump training: 10 times per group, three groups per day.Knee flexion and extension training: 10 times per group, three groups per day.Straight leg lifting training: 10 times per group and three groups per day.Hip abduction training inside lying position: adopt a healthy side-lying position, and slowly put down the affected hip after 5 ~ 10 s of abduction.Patellofemoral joint mobilization: the knee joint being fully extended with the leg muscles relaxed, the patella being loosened up, down, left, and right. These exercises were repeated 30 times for each group, and each direction could last about 10 s.Knee joint range of motion training: with the patient in the supine position, the healthy side of the lower limb was bent, the affected side of the lower limb was first relaxed and straightened, and the patient was then required to slide back, so that the knee joint could be flexed to an acceptable angle for 5 s, and then straightened 10 times per group, and three groups per day.Walking and stair climbing training: the walking distance and speed up and down stairs were gradually increased.Balance and proprioception training: the patient stands on the soft or hemispheric plane with eyes open or closed and maintains body balance for 30 s.

### Hamstring training group

The patients in the hamstring training group received routine rehabilitation treatment. Moreover, isokinetic eccentric training of the hamstring muscle was simultaneously added.

Preparatory activities before training: the hamstring muscle of the affected side of the patient should be relaxed and massaged for 5 min, and the patient should be guided to perform stretching exercises of the hamstring muscle to prevent discomfort during training.Isokinetic eccentric contraction training of hamstrings: Using the Biodex 4 isokinetic muscle strength training system (BIODEX, United States), the patient performed eccentric isokinetic training of hamstring muscle in the range of 20 ° ~ 80 ° of knee flexion on the affected side (15). The angular velocity was selected as 30°/s and 60°/s. Isokinetic eccentric hamstrings training was performed 10 times in each group, three training groups with an interval of 1 min. No active muscle movement was performed during eccentric knee joint reduction. Training should be terminated if the patient experiences discomfort or pain due to eccentric training.Relaxation activity after training: the hamstrings should be massaged and relaxed for 5 min after training.

### Study outcomes

The patients will be evaluated before rehabilitation training, after four weeks of training and four weeks after intervention (follow-up). Each evaluation will be performed by the same trained doctor for a comprehensive clinical examination and evaluation of outcome indicators. The evaluators will be blinded in this study and will be uninformed about the randomization of the participants or has the opportunity to participate in the research intervention. Adverse events will be recorded throughout the study.

